### Subject follow-up

The subjects will be followed up for a 2 year period. They will be selected at primary care doctor visits, when they will be asked to participate in the study. Once the patients have given their informed consent they will be given an appointment for the randomization visit and an appointment for the analytical tests and densitometry examination before starting treatment.

At the randomization visit the patient will be assigned to one of the study groups, their medical history will be taken, they will be given a physical examination and the study medicine will be dispensed. The following visits will be at 3, 6, 9, 12, 15, 18, 21 and 24 months. At these visits the efficacy (data on falls, fractures, muscle strength and mobility and musculoskeletal function) and safety (the detection of adverse effects) parameters will be collected, treatment compliance will be evaluated and the medication will be dispensed.

Discontinuation of treatment will be for the following reasons: completion of follow-up period (two consecutive years), death, violation of protocol, adverse event, inter-current illness causing immobilization for more than 30 days and patient abandoning trial or withdrawing informed consent.

### Definitions of the primary variables and measuring methods

The primary variable will be the incidence of spontaneous falls according to the FICSIT (Frailty and Injury: Cooperative Study of Intervention Techniques) definition: "Unintentionally coming to rest on the ground, floor, or other lower level. Coming to rest against furniture or a wall was not counted as a fall." Information on the circumstances of the fall (apparent cause, activity performed, time and place and need of help) will be obtained by an interview.

The following are the secondary variables:

- Consequence of falls (bone fractures at any location, need for healthcare, need for hospitalization, bed-ridden).

- Change in calcidiol [25(OH)D3] plasma levels (determined by RIA at baseline and at 6 and 18 months). Vitamin D deficiency is defined as a calcidiol plasma level lower than 10 ng/ml.

- Levels of transaminases, parathyroid hormone (PTH), calcium, phosphorous and serum creatinine, determined by tests on venous blood samples obtained in a fasted state. Calcium/creatinine index, determined by analysis of second morning urine.

- Change in bone mass (bone density or mineral content) obtained by densitometry (risk of fracture). Osteoporosis will be diagnosed based on a densitometry T-score of less than 2.5 in the vertebral column, according to WHO criteria.

- Change in muscle strength in the dominant hand. Determined by dyanometry (with a mean of 3 attempts to obtain a muscle strength measurement).

- Changes in musculoskeletal function, determined by the timed up and go test (the elderly person gets up from a chair with arms, walks three meters, turns round, walks back and sits down again). Taking more than 20 seconds indicates a high risk for falls.

- Stratification and potentially confounding variables; gender, age and other demographic data (social class, education level, marital status).

- Risk factors for falls: taking pre-disposing medication, health problems, toxic habits, physical exercise, living arrangements, sight or hearing difficulties, functional status (Katz index).

- Treatment compliance. To determine this, the patient will bring the medication containers (empty or partially empty) to each visit. According to their degree of compliance (difference between number of tablets dispensed and number of tablets consumed) the patients will be classified as normal compliers (89-100%), hypercompliers (> 110%) or hypocompliers (< 80%). Compliance will also be evaluated by the Morisky-Green test.

- Serious adverse events or any other adverse event. An adverse event is considered as any untoward medical occurrence in any patient included in the study which does not necessarily have a causal relationship with the treatment. An adverse event can therefore be any unfavorable and unintended sign (including an abnormal laboratory finding), symptom, or disease temporally associated with the use of a medicinal product. Known adverse events of the calcium vitamin D combination at the proposed doses are: occasionally slight gastrointestinal alterations and the possibility of stimulating kidney stone formation in patients with impaired renal function.

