**Methods/Design:**

Phase III, randomized, double blind, placebo-controlled trial to evaluate the efficacy of already marketed drugs in a new indication. It will be performed at Primary Care doctor visits at several Healthcare Centers in different Spanish Health Areas. A total of 704 non-institutionalized subjects aged 65 years or older will be studied (sample size calculated for a statistical power of 80%, alpha error 0.05, annual incidence of falls 30% and expected reduction of 30% to 20% and expected loss to follow up of 20%). The test drug containing 800 IU of vitamin D and 1000 mg of calcium will be administered daily. The control group will receive a placebo. The subjects will be followed up over two years. The primary variable will be the incidence of spontaneous falls. The secondary variables will include: consequences of the falls (fractures, need for hospitalization), change in calcidiol plasma levels and other analytical determinations (transaminases, PTH, calcium/phosphorous, albumin, creatinine, etc.), change in bone mass by densitometry, change in muscle strength in the dominant hand and change in musculoskeletal strength, risk factors for falls, treatment compliance, adverse effects and socio-demographic data.

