### Study objectives

The first objective is to determine the efficacy of calcium and vitamin D supplementation at doses of 1200 mg and 800 IU, respectively, to reduce the incidence of falls and fractures in non-institutionalized elderly people.

The second objective is to measure and compare treatment groups (calcium and vitamin D vs placebo) as regards muscle strength and musculoskeletal function, bone mineral density, calcidiol level and treatment safety.

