### Sample size

The sample size was calculated statistically to obtain a power of 80% with an alpha error of 0.05. In order to demonstrate an effect in calcium and vitamin D treated patients, consisting of a 30% to 20% reduction in the incidence of falls (relative risk reduction equivalent to 33%), a sample size of 586 (293 in the treatment group and 293 in the non-treatment group) is needed. Assuming a 20% loss to follow-up, 704 subjects between the two groups need to be selected. The two groups will be of equal size in order to obtain the greatest statistical power.

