## Discussion

If calcium and vitamin D supplementation is effective in the prevention of falls and fractures in the elderly population, a recommendation may be issued with the aim of preventing some of the consequences of falls that affect quality of life and the ensuing personal, health and social costs.

Using a randomization procedure will reduce selection bias as the investigator does not assign the treatment and any factor affecting participation will be equally divided between the two groups. Confounding is also reduced because randomization tends to share the determining factors that may affect the final result equally among the groups.

However, bias in the collection of information could occur in the study, such as patient evolution, determined by the aging process throughout the two study years, also the regression toward the mean or tendency of the continuous variables to approach the mean value in successive measurements. In our case this is applicable to the number of falls by the elderly people or the analytical test results. Furthermore, the participants, who are aware of the study objectives, could contribute to what is termed "hypothesis guessing" and try to downplay the importance of falls without consequences. There will also be a possible risk of differential loss to follow up between the groups being compared, due to the duration of the study and the placebo effect, which could contribute to patients abandoning the study because they consider the medication they are given is having no effect.

Follow-up visits with controls every 3 months will allow us to balance recommendations on treatment compliance and increase the possibility of detecting adverse effects. This will give us greater control over the development of the study.

As regards problems of external validity, the participants may not represent all eligible subjects if the rate of non responders were high. Furthermore, the study population characteristics (socio-economic level, life-style, etc.) may mean that the results cannot be directly transferred to any other population.

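### The first objective is the incidence of fractures, but the only fracture variable defined is fractures that follow a fall

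*Protocol article*

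**What the plan says.** Five places in the protocol article bear on this.

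- **Study objectives.** The first objective is for supplementation "to reduce the incidence of falls and fractures in non-institutionalized elderly people". Fractures stand beside falls, and nothing makes one conditional on the other.
- **Subject follow-up.** Among the data for every follow-up visit: "At these visits the efficacy (data on falls, fractures, muscle strength and mobility and musculoskeletal function". Fractures again stand as a separate item.
- **Definitions of the primary variables and measuring methods.** "The primary variable will be the incidence of spontaneous falls according to the FICSIT" definition, which adds: "Coming to rest against furniture or a wall was not counted as a fall". Fractures appear once as a variable, in the first secondary bullet: "Consequence of falls (bone fractures at any location, need for healthcare, need for hospitalization, bed-ridden".
- **Abstract, Methods/Design.** The secondary variables include "consequences of the falls (fractures, need for hospitalization", the same conditional form.
- **Discussion (and the abstract's Discussion).** A recommendation may follow if supplementation is "effective in the prevention of falls and fractures in the elderly population".

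**The concern.** The objective asks whether supplementation reduces fractures. The variable counts only fractures that follow a fall, and a fall in a restricted sense. The phrase about location widens the anatomical site, not the cause. Read as written, three kinds of event are outside the variable: a vertebral fracture with no fall, a fracture on lifting, and a wrist fracture in someone whose descent is stopped by a table.

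These events matter because the trial's rationale runs through bone as well as through falling. The Background links vitamin D insufficiency to osteoporosis and fracture, and the variable list includes densitometry as a marker of fracture risk. Fractures without a fall are where an effect on bone could show apart from an effect on falling. A conclusion about preventing fractures in general would rest on a partial count. Analysts could also choose between two defensible counts after seeing the data, because one section supports each.

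**Working it through.** **Step 1. Set the sections side by side.**

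| Section | How fractures appear | Conditional on a fall? |
|---|---|---|
| Study objectives | Incidence, beside falls | No |
| Subject follow-up | Own efficacy item at each visit | No |
| Definitions of the primary variables | Secondary variable, consequence of falls | Yes |
| Abstract, Methods/Design | Secondary variable, consequence of falls | Yes |
| Discussion; abstract Discussion | Prevention of falls and fractures | Not stated |

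The objective and the collection schedule are unconditional. The variable is conditional.

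**Step 2. See whether the analysis section repairs this.** Statistical analysis describes and compares the incidence of the variables in each group, which refers back to the variables already defined. Its time-to-event analysis is of the fall-free period. It names no fracture analysis independent of falls.

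**Step 3. Check whether the sample size is touched.** Inputs from Sample size: 30% versus 20% with a fall, equal groups, "to obtain a power of 80% with an alpha error of 0.05". Sidedness is not stated; two-sided is assumed.

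n per group = [z(0.975)·√(2·p̄(1−p̄)) + z(0.80)·√(p1(1−p1) + p2(1−p2))]² / (p1−p2)², with p̄ = 0.25

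= [1.960·√0.375 + 0.8416·√0.37]² / 0.10² = (1.2002 + 0.5119)² / 0.01 ≈ 293.2

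Rounded up this is 294 per group (588 in total), against the stated 293 (586). Power at 293 per group is 79.98%. The stated figure reproduces, and it rests on falls only. How fractures are defined does not enter it.

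**Step 4. Illustrate the fracture comparison.** Everything here except 293 per group and the 33% relative reduction is an assumption. Let p be the two-year control risk of any fracture and s the share that follows a qualifying fall. The one-third reduction planned for falls is applied to both kinds of fracture. The variable as written then compares p·s with (2/3)·p·s.

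Power = Φ[(d − 1.96·SE0)/SE1], where d is the difference in risk, SE0 the pooled and SE1 the unpooled standard error.

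Example, p = 5%, s = 75%: risks 3.75% and 2.50%, d = 0.0125, SE0 = √(0.03125·0.96875·2/293) = 0.01438, SE1 = √[(0.0375·0.9625 + 0.025·0.975)/293] = 0.01437. Power = Φ(−1.09) ≈ 14%.

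| Control risk p | All fractures (s = 100%) | s = 90% | s = 75% | s = 50% |
|---|---|---|---|---|
| 1% | 6% | 6% | 6% | 5% |
| 2% | 9% | 9% | 8% | 6% |
| 3% | 12% | 11% | 10% | 8% |
| 5% | 17% | 16% | 14% | 10% |
| 8% | 25% | 23% | 20% | 14% |

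In events, at p = 5% the two groups together would expect 293·(0.05 + 0.0333) ≈ 24 participants with any fracture. At s = 75% about 18 of them would be in the variable as written.

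**The case against.** The strongest reply is that this is a falls trial. The abstract's objective names musculoskeletal function and falls, not fractures. The primary variable and sample size are falls only. The Discussion follows its mention of fractures with a reference to the consequences of falls. Fractures could be read as fall-related throughout, with the objective worded loosely. That reading is coherent, and it is why narrowing the objective is an acceptable remedy. It does not remove the mismatch, because Study objectives and Subject follow-up both list fractures without the condition.

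Other objections stand in part:

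- **Bone is measured anyway.** Densitometry does capture an effect on bone density. It is not a count of fractures, which is what the objective names.
- **An all-cause count also mixes effects on falling and on bone.** True. Only the flag for fall-related or not would separate them.
- **This is a condensed article.** Confirmation, source of report and form layout can be left to the full protocol. The point here is not an omission: the article does define the variable, and that definition disagrees with its objective.

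A reader might infer more: that fractures without a fall go unrecorded, or that recording one depends on the patient reporting a fall. The documents do not support this. Fractures are listed separately at all eight follow-up visits, and the adverse-event definition would also cover them. Nor does the Discussion's worry about participants playing down falls help that inference. It concerns falls without consequences, and a fall that breaks a bone is not one of those.

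**Conclusion.** The point holds as a mismatch between objective and endpoint. The fracture objective is unconditional, while the only variable defined to answer it requires a qualifying fall. What is shown is exclusion from the defined variable, not loss of data.

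Its size cannot be taken from the documents. In the illustration, power for fractures is about 6% to 25% if all count and 5% to 14% if only half follow a qualifying fall. The comparison is weak either way, so the gain from correcting it is an answer to the question asked, not a decisive test. The illustration assumes control risks of 1% to 8%, a common relative reduction of 33%, 293 evaluable per group and a two-sided 5% test. The mismatch itself depends on none of these. The primary analysis and its sample size are unaffected. The change should be made, but it concerns a secondary variable.

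**What to change.** In Definitions of the primary variables and measuring methods, add a separate secondary variable: every new fracture after randomisation, regardless of cause, compared by randomised group. Flag each fracture as related to a qualifying fall or not, and keep the fall-related ones under consequences of falls as a subset.

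If the investigators intend only fall-related fractures, leave the variable as it is and limit Study objectives, the Discussion and the abstract's Discussion to fall-related fractures.

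The first route costs one extra field and one extra secondary analysis, since fracture data are already scheduled at every follow-up visit. The second costs only wording. Either should be settled before unblinding, so that which fractures count is not chosen after the results are known.

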## Background

Vitamin D insufficiency is common in older people [1] and is associated with several disorders related to aging such as osteoporosis, which leads to a significantly increased risk of bone fractures [2]. These are associated with physical disabilities, reduced quality of life, increased mortality and increase in healthcare costs [3]. According to the SENECA study [4], carried out in elderly people in 11 European countries, 47% of the elderly people had vitamin D deficiency (< 12 ng/ml). This deficiency was more common in Mediterranean countries than in Northern European countries, probably because in the latter countries there is a greater consumption of fish, fortified foods and vitamin D supplements.

According to several authors [5-10], vitamin D serum level is related to muscular strength, physical functional status and risk of fractures and falls, the annual incidence of which is around 30% in persons over 65 years [11]. It has been demonstrated that in institutionalized women, daily calcium and vitamin D supplementation decreases the number of falls and risk of fracture, increases bone mineral density and improves musculoskeletal function [12-14]. The conclusion in a Cochrane review [15], designed to determine the effect of vitamin D on the prevention of fractures in elderly people with senile or post-menopausal osteoporosis, is that the efficacy of this vitamin or of its analogues in the prevention of fractures remains unknown. A reduction in hip fractures in institutionalized, frail, elderly people was observed with the concomitant administration of calcium supplements, but the effect in community-dwelling, younger, healthy older adults was unknown.

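### Falls before entry are not named among the baseline covariates, although falls are the primary variable; naming and prespecifying them is a cheap, modest gain

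*Protocol article*

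**What the plan says.** The section Definitions of the primary variables and measuring methods makes the incidence of spontaneous falls, under the FICSIT definition, the primary variable. It then gives two covariate lists. The first holds stratification and potentially confounding variables: gender, age, social class, education level and marital status. The second reads "Risk factors for falls: taking pre-disposing medication, health problems, toxic habits, physical exercise, living arrangements, sight or hearing difficulties, functional status (Katz index". Falls before entry are in neither, and no other section of the article names a fall history.

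Subject follow-up assigns fall data to the visits at 3 to 24 months. At the randomisation visit, after the patient is assigned to a group, "their medical history will be taken, they will be given a physical examination and the study medicine will be dispensed". The content of that history is not given.

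Two other sections bear on a pre-entry fall measure. Statistical analysis begins by comparing the variables of interest, as well as the stratification and confounding variables, between the groups at the start of the study. It later stratifies on each independent variable to obtain an adjusted relative risk, and fits a Cox model. The Discussion describes regression toward the mean in successive measurements and adds: "In our case this is applicable to the number of falls by the elderly people or the analytical test results".

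**The concern.** The baseline value of an outcome is the most direct covariate for it. Here the two lists decide what the stratified analysis can adjust for, and that value is not on them. The start-of-study comparison and the regression-to-the-mean remark both make most sense if an earlier fall count exists, but the article defines none.

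Two modest things are at stake. The groups could not be compared at baseline on the variable that matters most to the primary result. The adjusted relative risk and the Cox model would also forgo whatever precision prior falls could add beyond the listed factors. If the item is not recorded at entry, it is hard to recover: recall weakens, and the answer no longer predates treatment.

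**Working it through.** **1. The plan's own figure.** Inputs from the Sample size section: "The sample size was calculated statistically to obtain a power of 80% with an alpha error of 0.05"; an effect "consisting of a 30% to 20% reduction in the incidence of falls (relative risk reduction equivalent to 33"%); result "a sample size of 586 (293 in the treatment group and 293 in the non-treatment group) is needed". The formula is n = (1.96 + 0.84)² × variance term / 0.10². A pooled-variance, two-sided test without continuity correction gives 294 per group, and unpooled variance gives 291. The stated 293 is reproduced, and power at 293 per group is 80.0%. Nothing below changes this figure.

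**2. Assumptions that are not in the documents.** 30% of participants fell in the year before entry. Prior fallers have RR = 1.5, 2, 2.5 or 3 times the risk of the others. The pooled risk during the trial is 25%, the mean of the planned 30% and 20%.

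**3. Variance explained by a yes/no prior fall.**
- Risk in those without a prior fall: p0 = 0.25 / (0.7 + 0.3 × RR).
- Risk difference between prior fallers and the rest: d = p0 × (RR − 1).
- R² = 0.3 × 0.7 × d² / (0.25 × 0.75).
- Effective size per group after adjustment: 293 / (1 − R²). Power is then recomputed for 30% vs 20%. This is a linear-model approximation to the gain in a stratified or Cox analysis.

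| RR | p0 | d | R² | Effective n per group | Power |
|---|---|---|---|---|---|
| 1.5 | 0.217 | 0.109 | 0.013 | 296.9 | 80.5% |
| 2 | 0.192 | 0.192 | 0.041 | 305.7 | 81.6% |
| 2.5 | 0.172 | 0.259 | 0.075 | 316.7 | 83.0% |
| 3 | 0.156 | 0.313 | 0.109 | 329.0 | 84.3% |

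**4. Chance imbalance, put in scale.** With 352 per group (704 / 2), the 95% range of the difference in the proportion of prior fallers is 1.96 × √(0.3 × 0.7 × 2 / 352) = 6.8 points. Multiplied by d, this moves the absolute risk reduction by 0.7 to 2.1 points. The 95% half-width of the absolute risk reduction itself is 1.96 × √((0.3 × 0.7 + 0.2 × 0.8) / 352) = 6.4 points. The shift is one component of that sampling error and is not added to it.

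**The case against.** **A condensed article.** The full protocol is not shown, and a fall history may already sit under the medical history at randomisation or under health problems. The baseline comparison and the regression-to-the-mean remark fit an item that is collected but not spelled out as well as one never collected. This stands. A reader might infer that the primary comparison cannot be adjusted for prior falls, but the article does not establish that. It shows only that an explicit covariate list leaves the item out while other sections lean on it.

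**Validity.** A reader might infer that an imbalance in prior fallers would bias the result. It would not. Randomisation makes such imbalance part of sampling error, already inside the planned confidence intervals (step 4).

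**The planning incidence.** The Background gives the figure for older people at large: "the annual incidence of which is around 30% in persons over 65 years". The trial applies further selection criteria, so a reader might infer that the 30% cannot be checked in those enrolled, or that power falls short. Neither follows. Falls are collected every three months, so blinded pooled counts can check the rate during follow-up. The 30% is annual and follow-up lasts two years, so a lower annual rate cannot be read as the whole-trial rate. For example, 20% per year with a one-third annual reduction gives 1 − 0.80² = 36.0% against 1 − 0.867² = 24.9% over two years. Power is then about 83% at 293 per group, assuming independent years; correlation between years would lower it. The documents give no fall rate for the enrolled population.

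**Size.** The gains in step 3 are ceilings for prior falls taken alone. The Katz index, medication, health problems, exercise, sight or hearing and the timed up and go test are already recorded and may carry part of the same information. This also stands.

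**Conclusion.** The point holds as a covariate improvement and not as an error in the primary comparison. The article's explicit lists do not name falls before entry, although the planned start-of-study comparison and the regression-to-the-mean remark both call for such a measure. The loss is a baseline check on the primary variable and, under the assumptions of step 2, between half a point and about four points of power, less whatever the other listed covariates already supply. No stated figure in the article is wrong on this account, and the sample size does not need to change because of it.

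**What to change.** At the randomisation visit, ask for the number of falls in the previous 12 months in the FICSIT wording, and record the answer before assignment, since the article mentions assignment first and history second. If a fall history is already collected, state where and with what definition and look-back period. Add the item to the list of fall risk factors. Prespecify it in categories (0, 1, 2 or more) as a baseline covariate in the Cox model and as a stratum for the adjusted relative risk, and include it in the start-of-study comparison.

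The cost is one question on the baseline form and one line in the analysis plan. The answer relies on recall and is therefore imperfect. Because it is taken before assignment, recall error cannot differ systematically between the groups; it only reduces the precision gained.
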